#### Sham–control HD-tDCS droup

The procedure for sham stimulation will be identical, except that the electrical current will be gradually ramped down to zero after the first 30 s, thus giving the same initial sensation of HD-tDCS. The stimulator will be programmed to switch the current on and off, so no intervention by the operator will be required. The computer will be placed behind the subjects’ heads so they cannot see the readout.

### Criteria for discontinuing or modifying allocated interventions {11b}

The intervention will be terminated upon the patients’ request.

### Strategies to improve adherence to interventions {11c}

To reduce the drop-out rate, each of the participants’ case medical officers will be alerted to remind the participants to attend all interventions and assessments. In addition, the benefits and side effects of HD-tDCS will be clearly explained during enrolment, and materials related to this study will be provided to both the participants and their caregivers. The participants and their caregivers will receive two reminder telephone calls (1 week and 1 day) before interventions and assessments. If a participant fails to attend an appointment, they will be called to rearrange the appointment. A direct hotline within office hours will be provided to the participants and their caregivers in case of any concerns or problems.

### Relevant concomitant care permitted or prohibited during the trial {11d}

All participants will be instructed to continue their pre-existing regimen of psychiatric medications, including antidepressants, benzodiazepines, hypnotics, for at least 4 weeks before the intervention until all post-intervention assessments are complete. Medication adherence will be recorded during each assessment.

### Provisions for post-trial care {30}

All participants will be continued to follow up by the case medical doctors in psychiatric outpatient clinics for their progress.

### Outcomes {12}

#### Baseline assessments

##### Diagnostic interview

Diagnoses will be confirmed with a semi-structured psychiatric diagnostic assessment using the validated Chinese-bilingual version of the Structured Clinical Interview for DSM Mental Disorders by an experienced psychiatrist according to DSM-V.

##### Demographic data

The subjects’ basic demographic data, including age, gender, years of education, place of birth, marital status, number of children, financial condition, family history of affective disorder and household income, will be collected upon study entry. Medical comorbidities will be assessed with the Cumulative Illness Rating Scale. The handedness of the participants will be evaluated using the Edinburgh Handedness Inventory – Short Form. Details of the subjects’ psychiatric history, including the age of onset of the first depressive episode, the number of relapse episodes and current medication and dosage, will also be recorded at the baseline assessment. The medical health history and treatment will be assessed by direct enquiry with the patients and confirmed with their electronic health record in the hospital authority.

##### Primary outcome

The primary outcome will be the change of depressive symptoms, the clinical response rate and the remission rate as measured with the HAMD-17 at 12 weeks after the completed intervention. HAMD-17 is a widely used and reliable measure of depressive symptoms [21]. Scores range from 0 to 52, with higher scores indicating more severe depression. A clinical response will be defined as a reduction of 50% or more in the HAM-D-17 score in old age adult patients. A HAMD-17 score of 7 or less will be used as an indicator of remission [20].

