**Methods:**

Fifty-eight patients with LLD will be recruited and randomly assigned to the active HD-tDCS or sham HD-tDCS group. In both groups, patients will receive the active or sham intervention in addition to their pre-existing antidepressant therapy, for 2 weeks with 5 sessions per week, each lasting 30 min. The primary outcome measures will be the change of depressive symptoms, clinical response and the remission rate as measured with the Hamilton Depression Rating scale (HAMD-17) before and after the intervention, and at the 4th and 12th week after the completed intervention. Secondary outcome measures include cognitive symptoms, anxiety symptoms, daily functioning and adverse effects.

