## Data collection and management

### Plans for assessment and collection of outcomes {18a}

A trained clinician investigator who is not involved in the intervention or randomization procedure will perform the assessments. The primary and secondary outcomes will be assessed at baseline, immediately after the intervention, and 4 and 12 weeks after the intervention.

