## Statistical methods

### Statistical methods for primary and secondary outcomes {20a}

The primary outcome measurement is HAMD-17. The effect power of intervention is measured by the change of HAMD-17. If the results showed a significant improvement in the HAMD-17 measurement, it represents the intervention is effective. Both clinical response rate and remission rate are also depending on the measurement of HADM-17. They are used as an indication for the real clinical impact of the intervention. A clinical response will be defined as a reduction of 50% or more in the HAM-D-17 score. A HAMD-17 score of 7 or less will be used as an indicator of remission. Therefore, a significant result in the area of either clinical response or remission rate will indicate the clinical impact of the intervention.

To examine the presence of any group differences in demographics and clinical profile between the treatment and the sham groups at baseline, chi-squared tests and *t*-tests will be performed for categorical and continuous variables respectively.

Two-way repeated measures analysis of variance (ANOVA) will be used to examine the effect of time and treatment conditions on the HAM-D-17 scores and other cognitive and IADL measurements across various assessment time points. The analysis would be adjusted to age, sex, medication type/dose, relapse episodes and other potential confounders. If both depressive symptoms and cognitive function improved, mediation analysis will be done to determine the cognitive function improvement is mediated by the improvement of depressive symptoms or vice versa.

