### Methods for additional analyses (e.g. subgroup analyses) {20b}

Post hoc analyses will also be performed with Bonferroni corrected t-tests to investigate the improvements in all outcome variables in pairwise comparisons across various assessment time points. Statistical significance will be set at a *p* value < 0.05. Intention-to-treat last-observation carried-forward scores will be used for the analyses. All computations will be performed using SPSS for Windows, version 22.0.

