## Discussion

This is the first RCT that evaluates the effectiveness and tolerability of HD-tDCS in older adults with depression. Most studies tend to assess effectiveness in the adult population and only a few studies have evaluated the effects of tDCS on cognitive function in depression.

This randomized controlled trial aims to evaluate the effectiveness of HD-tDCS as augmentation therapy with antidepressants in ameliorating depressive symptoms in patients with LLD who had a suboptimal response to treatment. To this aim, the trial compares the effect of HD-tDCS and sham-control HD-tDCS on improving depressive symptoms in addition to the pre-existing antidepressant regimen. The depressive symptoms are operationalized into three levels, namely the change of depressive symptoms, the clinical response and the remission rate measured by HAMD-17. Secondary objectives are to examine the intervention impact on the cognitive function, anxiety symptoms, daily functioning and adverse effects at the end of the intervention. We also plan to detect any sustained effect by checking the changes at the 4th week and 12th week after the finished intervention.

The results from this trial will be useful for the management of patients with LLD because a new safe treatment option is needed to alleviate depressive symptoms for those showing suboptimal responses to conventional antidepressants. It is also expected that HD-tDCS is effective in improving cognitive function which is often significantly impaired in LLD. Based on its effect on neural plasticity and enhancement of serotonin and cognitive function, our study aims at confirming the efficacy of HD-tDCS as augmentation therapy for antidepressants in patients with LLD.

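### The primary HAMD-17 time point is not stated consistently, and the named repeated-measures ANOVA does not test the week-12 group difference

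*Protocol article*

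**What the plan says.** All places are in the protocol article.

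- **Outcomes {12}, Primary outcome:** HAMD-17 change, response rate and remission rate are primary "as measured with the HAMD-17 at 12 weeks after the completed intervention".
- **Abstract, Methods:** the same three measures are primary, taken "before and after the intervention, and at the 4th and 12th week after the completed intervention". No visit has priority.
- **Plans for assessment and collection of outcomes {18a}:** outcomes are "assessed at baseline, immediately after the intervention, and 4 and 12 weeks after the intervention". This is a schedule and conflicts with nothing by itself.
- **Statistical methods for primary and secondary outcomes {20a}:** "Two-way repeated measures analysis of variance (ANOVA) will be used to examine the effect of time and treatment conditions on the HAM-D-17 scores", together with "other cognitive and IADL measurements across various assessment time points". The same section treats a significant HAMD-17 improvement as showing that the intervention works. It does not say at which visit or by which comparison.
- **Methods for additional analyses {20b}:** "Post hoc analyses will also be performed with Bonferroni corrected t-tests", comparing assessment time points for all outcome variables.
- **Discussion:** "We also plan to detect any sustained effect by checking the changes at the 4th week and 12th week after the finished intervention".

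**The concern.** Week 12 appears as the sole primary visit in one place and as one of several unranked visits in another. In a third it can be read as a follow-up check. The named analysis does not resolve this. The F-tests for group and for group by time pool or compare all four visits, and neither isolates the active-versus-sham difference at week 12. An effect that is present at the end of the two treatment weeks and gone by week 12 could produce a significant interaction. Under the success statement as written, that could be reported as success on an outcome defined at week 12.

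**Working it through.** **Inputs from the article.** Four visits ({18a}); 24 evaluable patients per group and a standardised effect of 0.743 (Sample size {14}). The article gives no numerical result for the primary time point, so there is no figure to reproduce on this point.

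**Assumptions, not in the article.** SD 1 at every visit; equal correlation ρ between visits, tried at 0.3, 0.5 and 0.7; complete data; no covariates; two-sided 5%; and the effect patterns below. Let δ be the group difference in SD units at baseline, end of treatment, week 4 and week 12.

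**Formulas (n = 24 per arm).**
- Group-by-time F-test: noncentrality λ = (n/2) × Σ(δ − mean δ)² / (1 − ρ), on 3 and 3 × 46 = 138 degrees of freedom, critical value 2.67.
- Week-12 change contrast: d = δ(week 12) / √(2(1 − ρ)), noncentrality d × √(n/2), on 46 degrees of freedom.

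**1. Effect that fades: δ = (0, 0.743, 0.37, 0).** The mean is 0.278 and the sum of squared deviations is 0.379, so λ = 12 × 0.379 / (1 − ρ).

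| ρ | λ | Interaction significant | Week-12 change contrast |
|---|---|---|---|
| 0.3 | 6.50 | 54% | 5% |
| 0.5 | 9.10 | 70% | 5% |
| 0.7 | 15.17 | 91% | 5% |

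Simulation gives the same picture (53% to 92% over this range of ρ). The group main effect is significant in 28%, 22% and 19% of trials.

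**2. Effect that builds: δ = (0, 0.2, 0.4, 0.743).** The mean is 0.336 and the sum of squares is 0.301. λ is 5.16, 7.23 and 12.05, so the interaction has 44%, 59% and 83% power. For the week-12 change contrast, d is 0.628, 0.743 and 0.959, and power is 57%, 71% and 90%. Simulated values agree within two percentage points (46/59/82% against 57/71/89%).

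**3. Effect sustained at 0.743 SD at all three post-baseline visits, or present at week 12 only.** Both patterns have sum of squares 0.743² × 3/4 = 0.414. λ is 7.10, 9.94 and 16.56, so the interaction has 58%, 74% and 94% power, against 57%, 71% and 90% for the change contrast. Nothing is lost relative to that contrast.

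**4. Baseline-adjusted contrast at week 12.** With d = 0.743 / √(1 − ρ²) and 45 degrees of freedom, power is about 75%, 83% and 94%.

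**The case against.** Several points on the other side are fair.

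- **The Abstract may only be listing measurement times.** Its list includes baseline, which cannot be an endpoint, so it resembles the schedule in {18a}. That is a reasonable reading. The sentence is nevertheless the Abstract's definition of the primary outcome, and it leaves out the priority that the Outcomes section gives to week 12.
- **The Discussion sentence may concern secondary outcomes.** It directly follows the secondary objectives. It supports the point but cannot carry it.
- **The ANOVA is not the only test stated.** {20b} adds Bonferroni-corrected t-tests, which might include a week-12 comparison. They are labelled post hoc and described as comparisons across time points, and nothing designates one as the primary test.
- **The fading pattern is chosen.** The open-label pilot, as described in the article, found an effect still present at one and three months. The pattern here shows what the test can do and is not a forecast.
- **The choice of contrast may sit in the analysis plan, which is not shown.** Missing detail would be no finding. The point here is that the article's own statements do not agree, and that the test it names does not match the outcome it defines.

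A reader might also infer two stronger things that the article does not support. The first is an inflated false-positive rate of about 12% to 13% from three candidate visits. That needs uncorrected choice among visits after the results are seen. The stated plan is one ANOVA, whose interaction holds about 5% under the null, followed by Bonferroni-corrected tests, which give about 4% to 5% over three visits.

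The second is that the sample size was computed for a different test. The Sample size section names no test. A one-sided 5% two-sample t-test with 24 per group gives 81.3% power. A four-visit ANOVA group effect with ρ = 0.7 gives 81.7% with the same 48 patients. The article does not decide between them.

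**Conclusion.** The point holds. The Outcomes section and the Abstract do not define the primary time point in the same way, and the named HAMD-17 analysis does not answer the week-12 question. In the fading illustration, the interaction is significant in just over half to about nine in ten trials although no week-12 difference exists. The exact share rests on the assumed correlation, effect pattern and complete data; last observation carried forward and the planned covariates were not modelled. The qualitative conclusion is the same at all three correlations tried.

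A general claim that the ANOVA costs power does not hold. Compared with the change contrast, it loses power in the building pattern and loses none in the sustained or week-12-only patterns. The case rests on interpretation: a significant interaction cannot be read as a week-12 effect.

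**What to change.** Before unblinding:

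1. State one primary time point in the same way in the Abstract, the Primary outcome section, {20a} and the Discussion. Keep week 12, as the Primary outcome section has it. If the sponsor intends end of treatment, change that section instead.
2. In {20a}, make the primary test the baseline-adjusted active-versus-sham HAMD-17 contrast at that visit, from a mixed model for repeated measures or an ANCOVA. Tie the success statement to that contrast.
3. List the other visits as secondary.

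The cost is wording and a changed model statement. All visits are already scheduled, and {21b} places the analysis after the trial. The downside is that, with week 12 as primary, an early effect becomes a secondary result. The contrast covers the HAMD-17 score only; response and remission, which the Primary outcome section also sets at week 12, need their own stated comparison at the same visit.

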##### Secondary outcomes

Cognition

Global cognition will be measured using the Hong Kong Chinese version of the Montreal Cognitive Assessment (HK-MoCA) [22]. HK-MoCA is a cognitive screening test designed to assist health professionals to evaluate the cognitive functions of the patients. This encompasses the evaluation of visuospatial and executive functions, naming of object, memory, attention, language, abstraction, delayed recall and orientation. After completion of the test, the score in each domain will be documented and a total score out of 30 will be calculated for each participant. Working memory, executive function and attention will be measured by forward and backward digit span, the Stroop test, the category verbal fluency test and the Trail Making Test Parts A and B.2.Anxiety symptoms

Anxiety symptoms which commonly co-existed in depression will be measured by the Hamilton Anxiety Rating Scale (HAMA). It is a widely used clinician-rated scale. The HAMA is composed of fourteen items, including anxious mood, tension, fears, insomnia, intellectual, depressed mood, somatic (muscular), somatic (sensory), cardiovascular symptoms, respiratory symptoms, gastrointestinal symptoms, genitourinary symptoms, autonomic symptoms, and behaviour at interview. Each item is scored on a scale of 0 (not present) to 4 (severe), with a total score range of 0–56, where < 17 indicates mild severity, 18–24 mild to moderate severity and 25–30 moderate to severe [23]. Higher marks represent more severe in anxiety symptoms.3.Daily functioning

Instrumental activities of daily living will be assessed with the Hong Kong Chinese version of the Lawton Instrumental Activities of Daily Living Scale (IADL-CV) [24]. IADL-CV has been shown to be a valid and reliable tool for assessing an older person’s ability to live independently in the community. It encompasses the assessment of nine items, including telephoning, transportation, shopping, meal preparation, housework, handywork, laundry, medication and finance. For each domain, the patient’s IADL would be assessed by a four-point rating scale, with a total score ranging from 0 to 27. A higher score indicates a higher functioning level.4.Adverse effects and risk indicators

A checklist of potential adverse effects associated with t-DCS administration will be generated from the available literature [25, 26]. The checklist will be used to monitor tolerability and adverse events in each session throughout the intervention (attached). Risk indicators such as suicidal risk or severe self-neglect that would necessitate immediate changes to treatment will be directly assessed according to the risks and needs.

### Participant timeline {13}

The participant timeline of the HD-tDCS intervention is shown in Fig. 1.

**Fig. 1 Fig1:**
[figure not shown]
Flowchart of the current study

### Sample size {14}

The sample size was estimated using G*Power 3.1, based on the results of a tDCS meta-analysis of adult subjects by Kalu et al. [27]. In this study, active tDCS was found to be more effective than sham tDCS for the reduction of depression severity (Hedges’ g = 0.743). For 80% power and an alpha level of 5%, 48 patients (24 in each group) will be needed to detect group differences. To allow for a 20% drop-out rate, 58 patients (29 in each arm) will be recruited.

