## Assignment of interventions: allocation

### Sequence generation {16a}

Block randomization will be used in this study. Each block will consist of eight participants at a 1:1 ratio between the two groups. In the randomization procedure, each participant will be assigned a special number generated by a computer. These numbers will not be decoded until the intervention group is assigned.

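### The 80% power at 24 per group is derived for a difference in means only, yet the response and remission rates are also named primary and have clearly less power under the same assumed effect

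*Protocol article*

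**What the plan says.** In the protocol article, Sample size {14} takes one effect size from a meta-analysis of tDCS in adults: "active tDCS was found to be more effective than sham tDCS for the reduction of depression severity (Hedges’ g = 0.743". From this it concludes: "For 80% power and an alpha level of 5%, 48 patients (24 in each group) will be needed to detect group differences". It then adds the drop-out allowance: "To allow for a 20% drop-out rate, 58 patients (29 in each arm) will be recruited". The software is named ("The sample size was estimated using G*Power 3.1"), but the test and its sidedness are not. The general threshold in {20b}, "Statistical significance will be set at a *p* value < 0.05", gives no sidedness either.

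The Primary outcome section names three quantities: "The primary outcome will be the change of depressive symptoms, the clinical response rate and the remission rate as measured with the HAMD-17". Response is a fall of at least half in the score, and remission is a score of 7 or less. The Abstract lists the same three as primary measures, and the Discussion treats them as three levels of the depressive outcome.

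The statistical methods section {20a} calls HAMD-17 the primary measurement and measures the effect by its change. It presents the two rates as showing real clinical impact and gives them a criterion: "a significant result in the area of either clinical response or remission rate will indicate the clinical impact of the intervention".

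**The concern.** A standardised mean difference sizes a comparison of means. Response and remission are yes/no outcomes cut from the same scale, and cutting a scale discards information. The same true effect is therefore harder to detect on a rate than on the mean. The sample size section speaks of group differences without restricting the claim to one outcome, while two of the three named primary outcomes have no rate, no rate difference and no power calculation behind them.

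At stake is how the result is read. A reader who takes the sample size section together with the list of primary outcomes will credit all three with 80% power, and will give a non-significant response or remission comparison more weight than 24 patients per group can support.

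**Working it through.** **Inputs from the article.** g = 0.743; alpha 5%; power 80%; 24 per group; 1:1 allocation ("Each block will consist of eight participants at a 1:1 ratio between the two groups"); 29 per arm recruited.

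**Assumptions, because the article gives no figures.** Sham success rate 10-60%. The 0.743 SD shift applies between two normal distributions at whichever cut-point defines success. The test is an uncorrected Pearson chi-squared test.

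**1. The plan's own figure.** For two means, n per group = 2(z_alpha + z_beta)² / g², with g² = 0.552.

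- One-sided: 2 × (1.645 + 0.842)² / 0.552 = 22.4, so 23. The t-test solution is 23.1, so 24. Power at 24 is 81.3%.
- Two-sided: 2 × (1.960 + 0.842)² / 0.552 = 28.4, so 29. The t-test solution is 29.4, so 30. Power at 24 is 71.2%.

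The printed 24 per group thus reproduces from a t-test of means, but only one-sided. A between-group repeated-measures calculation can also give 48 in total, but it needs an assumed correlation of about 0.7, which the article does not state.

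**2. The same effect on a rate.** Active rate p1 = Φ(Φ⁻¹(p0) + 0.743). Example with p0 = 30%: Φ(−0.524 + 0.743) = Φ(0.219) = 58.7%. The pooled rate is 44.35%, and the standard error is √(0.4435 × 0.5565 × 2/24) = 0.143. The expected z is 0.287 / 0.143 = 2.0, which barely exceeds the two-sided critical value of 1.96.

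Exact binomial enumeration at 24 per group, for one rate:

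| Sham rate | Active rate | Power, two-sided | Power, one-sided |
|---|---|---|---|
| 10% | 29.5% | 41.7% | 54.1% |
| 20% | 46.1% | 49.9% | 61.5% |
| 30% | 58.7% | 55.2% | 66.6% |
| 35% | 64.0% | 56.0% | 67.3% |
| 40% | 68.8% | 55.5% | 66.9% |
| 50% | 77.1% | 51.7% | 63.4% |
| 60% | 84.0% | 47.4% | 58.9% |
| *Mean, t-test* | | *71.2%* | *81.3%* |

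**3. Loss on equal sidedness.** One-sided: 81.3 − 67.3 = 14.0 to 81.3 − 54.1 = 27.2 points. Two-sided: 71.2 − 56.0 = 15.2 to 71.2 − 41.7 = 29.5 points.

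**4. Sensitivity.** For sham rates of 10-50%:

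- Fisher's exact test, two-sided: 30-44%.
- A logistic instead of a normal conversion of g: 41-62% two-sided and 53-74% one-sided.
- Needed for 80% power on one rate: about 46-65 per group two-sided, or 36-51 one-sided.

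If all 29 per arm are analysed, over sham rates of 10-60%, one rate has 47-60% two-sided and at most 71% one-sided.

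**5. The rule that either rate may be significant.** Simulation used the same shift, sham rates of 10-40% for each rate and a latent correlation of 0.3-0.9 between them. At 24 per group, the chance that at least one rate is significant is about 54-78% two-sided and 67-87% one-sided. At 29 per group it is about 60-81% and 74-89%. With two uncorrected 5% tests, the false-positive chance would be 1 − 0.95² = 9.75% if they were independent. It is lower as they correlate.

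**The case against.** The strongest reply is that the article never claims 80% for the rates. In the sample size section the phrase about group differences directly follows the sentence on severity, and {20a} measures the effect by HAMD-17 change. Sizing on the continuous outcome and treating derived rates as clinical context is common practice. That reading is fair. However, the Abstract and the Primary outcome section list the rates as primary and nothing demotes them, so the power statement needs a limit that it does not have.

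Three stronger readings are tempting and should not be drawn.

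- *Setting 42% against 80%.* This compares a two-sided test with a figure that holds only one-sided. Part of that gap is sidedness, not dichotomising.
- *Calling the clinical-impact criterion a coin toss.* The criterion in {20a} accepts either rate and so has more power than one rate alone. One-sided it can exceed 80%. It gains this through a second uncorrected test, and the sample size section does not calculate it.
- *Inferring that a non-significant rate will be declared no clinical impact.* The text says only what a significant rate shows and gives no rule for the converse.

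It also stands that the rate figures rest on assumptions. One shift is applied to a percentage-change cut and to an endpoint-score cut alike. Since entry starts at a HAMD-17 of 8 and remission is 7 or less, a patient entering at 8 remits with a one-point fall, so a common shift is a simplification.

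**Conclusion.** The point holds as a matter of what the stated power covers. The 24 per group is a correct one-sided result for a difference in means. It does not carry over to the two rates that are also named primary. The exact percentages depend on the unstated sham rate, the common shift and the choice of test, and should be read as a range. The direction does not depend on them: no variant tried for a single rate at 24 or 29 per group reaches 80%. The either-rate criterion can reach it in some settings, without control of its error rate.

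**What to change.** - **Sample size {14}:** state that the size and power apply only to the between-arm difference in mean HAMD-17 change. State the sidedness used, noting that two-sided power at 24 per group is about 71%. Say that response and remission are not powered at 80%, and give their power on the same sidedness with the assumed sham rates shown.
- **Outcomes {12}, statistical methods {20a}, Abstract and Discussion:** make HAMD-17 change the single powered primary outcome. Report response and remission as supportive between-arm risk differences with 95% confidence intervals, in place of the criterion that either be significant. All four places need the edit, or the article will contradict itself.
- **Timing:** record the change as a dated amendment before unblinding. Recruitment was already under way at this protocol version, so this is a change of primary outcome during the trial and goes to the ethics committee under {25}.

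The cost is that two outcomes lose primary status, an amendment must be reported, and a less favourable power figure is printed. Enrolment and data collection do not change.

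### For a simple two-group comparison, 24 per group gives 80% power only at a one-sided 5% level; two-sided, the stated inputs give about 71% with 48 evaluable patients and at most about 79% with all 58

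*Protocol article*

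**What the plan says.** The Sample size section {14} names G*Power 3.1 and takes a Hedges' g of 0.743 from a meta-analysis of tDCS in adults. It then states: "For 80% power and an alpha level of 5%, 48 patients (24 in each group) will be needed to detect group differences". Recruitment is raised from there: "To allow for a 20% drop-out rate, 58 patients (29 in each arm) will be recruited". The section names no test family, does not say whether alpha is one- or two-sided, and gives no number of measurements, correlation or covariate gain.

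On the analysis side, section {20a} says: "Two-way repeated measures analysis of variance (ANOVA) will be used to examine the effect of time and treatment conditions", applied to HAMD-17 and other measures and adjusted for age, sex, medication, relapse episodes and other potential confounders. Section {20b} says: "Statistical significance will be set at a *p* value < 0.05", and prescribes an intention-to-treat analysis with last observations carried forward. The Primary outcome section places the primary outcome 12 weeks after the intervention ends. Allocation is 1:1 (section {16a}).

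**The concern.** The sample size and the analysis appear to use different thresholds. An ANOVA F test does not distinguish the direction of a difference; for two groups, the F test of the group effect on one degree of freedom is the two-sided t-test squared. If 24 per group was obtained at a one-sided 5% level, the trial was sized for a more lenient test than the one it will run.

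What is at stake is how a non-significant result is read. The background section describes conflicting tDCS trials, including a large null one, and the pilot section justifies this trial by the need for an adequate sample size. Readers would take a null result as coming from a trial with a 20% chance of missing the assumed effect. If the true chance is nearer 30%, that reading is too confident.

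**Working it through.** **Inputs.** From Sample size {14}: d = 0.743, alpha = 0.05, target power 0.80, n = 24 per group, 20% drop-out, 58 recruited. From Sequence generation {16a}: 1:1 allocation. Sidedness is not stated, so both cases are computed.

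**Formula.** Two-sample t-test with the noncentral t distribution: degrees of freedom 2n − 2, noncentrality d × √(n/2), critical value t(1 − α) one-sided or t(1 − α/2) two-sided. Power is the probability that the noncentral t exceeds the critical value (plus the negligible opposite tail when two-sided).

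**Reproducing the plan's figure.** At n = 24 the noncentrality is 0.743 × √12 = 2.574 on 46 degrees of freedom.

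| n per arm | Power, one-sided 5% | Power, two-sided 5% |
|---|---|---|
| 23 | 79.8% | 69.3% |
| 24 | 81.3% | 71.2% |
| 29 | 87.5% | 79.4% |
| 30 | 88.5% | 80.8% |

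One-sided, 23 falls just short and 24 is the smallest adequate size, which is exactly the printed figure. Two-sided, the smallest adequate size is 30 per arm (60 evaluable).

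**Number analysed.**
- 48 evaluable (24 per arm): 71.2%, so a type II error of 28.8%.
- 58 less 20%: 58 × 0.8 = 46.4, about 23 per arm: 69.3%, so a type II error of 30.7%.
- All 58 analysed (29 per arm): 79.4%.

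**Detectable effect.** Solving for the d that gives 80% two-sided power at 24 per arm yields 0.826, against the assumed 0.743.

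**Can another calculation give 48?** For the between-groups effect in a repeated-measures ANOVA, f = d/2 = 0.3715 and λ = N f² m / (1 + (m − 1)ρ), with 1 and N − 2 degrees of freedom, m measurements and correlation ρ. Both m and ρ have to be assumed.

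| m | ρ | Smallest even N for 80% | Power at N = 48 |
|---|---|---|---|
| 2 | 0.6 | 48 | 80.4% |
| 3 | 0.7 | 48 | 80.4% |
| 4 | 0.7 | 48 | 81.7% |
| 2 | 0.5 | 46 | 82.9% |
| 3 | 0.5 | 40 | 87.0% |
| 4 | 0.5 | 38 | 89.0% |

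So 48 is attainable non-directionally, but only for particular pairs of m and ρ.

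**Covariate adjustment.** If the covariates correlate with the outcome at r (assumed), d is replaced by d/√(1 − r²). At 24 per arm, two-sided power is 75.2% for r = 0.3, 80.6% for r = 0.45 and 82.9% for r = 0.5.

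**The case against.** The best defence has four parts.

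*Sidedness is unstated, so nothing is strictly contradicted.* It is true that the two-sided reading is inferred. It rests on the efficacy F test alone: the chi-squared and t-tests in {20a} compare baseline characteristics, and the Bonferroni t-tests in {20b} are post hoc comparisons between time points. But the paragraph needs correcting either way. If alpha is two-sided, 24 is too few for a two-group t-test; if it is one-sided, the sample size rests on an undeclared one-sided level that the planned F test does not use. Calling the trial a superiority trial does not make its test one-sided.

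*The calculation may have been a repeated-measures one.* This stands in part. A reader might infer from the exact match that the sponsor must have used a one-sided t-test, and that 80% can be reached in no other way. The document does not support that, because it does not name the G*Power module and some repeated-measures inputs also give 48. Those inputs appear nowhere in the protocol, however, and that route powers a group difference averaged over visits, whereas the primary outcome is placed at 12 weeks.

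*All 58 are analysed.* This also stands in part. A reader might take 71% as the power of the trial as such. Under intention-to-treat with carried-forward scores, drop-outs stay in the analysis, and nominal power at 29 per arm is 79.4%, close to the claim. That is an upper figure for the unadjusted test: carried-forward scores may dilute the difference, and the Trial design section says 48, not 58, will be randomised.

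*Covariate adjustment recovers power.* It may, with covariates of moderate prognostic strength. But the Sample size section claims no such gain and gives no correlation.

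**Conclusion.** The concern holds for the inputs that the protocol prints. As a two-group comparison, 24 per group delivers 80% power at g = 0.743 only with a one-sided 5% level, which is nowhere declared and does not fit the planned F test. Two-sided power for the unadjusted comparison lies between about 69% and 79%, depending on how many of the 58 contribute data, with 71% at the protocol's own figure of 48. At 46 to 48 evaluable patients the risk of missing the assumed effect is about 29–31%, not 20%.

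This rests on three assumptions: the efficacy test is two-sided at 5%, g = 0.743 is the true standardised difference at the time point tested, and no power is gained from repeated measures or covariates. It does not show that the trial cannot reach 80% under some other analysis. It shows that the stated 80% does not follow from what is stated.

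**What to change.** Restate the sample-size paragraph, for example:

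> For an unadjusted two-sided 5% two-group comparison, 48 evaluable patients give about 71% power for g = 0.743 (80% power for g = 0.83); analysing all 58 gives about 79%.

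If a repeated-measures or covariate-adjusted calculation was in fact used, state the G*Power module, the number of measurements, the assumed correlation and the resulting power, and say which effect (time-averaged or at 12 weeks) it refers to. The figure should not be rescued by declaring a one-sided test now.

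The change is to wording only. It requires no extra patients and no change to the analysis; the cost is a less favourable stated power.
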